## Abstract

Novel techniques, such as microwave imaging, have been implemented in different prototypes and are under clinical validation, especially for breast cancer detection, due to their harmless technology and possible clinical advantages over conventional imaging techniques. In the prospective study presented in this work, we aim to investigate through a multicentric European clinical trial (ClinicalTrials.gov Identifier NCT05300464) the effectiveness of the MammoWave microwave imaging device, which uses a Huygens-principle-based radar algorithm for image reconstruction and comprises dedicated image analysis software. A detailed clinical protocol has been prepared outlining all aspects of this study, which will involve adult females having a radiologist study output obtained using conventional exams (mammography and/or ultrasound and/or magnetic resonance imaging) within the previous month. A maximum number of 600 volunteers will be recruited at three centres in Italy and Spain, where they will be asked to sign an informed consent form prior to the MammoWave scan. Conductivity weighted microwave images, representing the homogeneity of the tissues’ dielectric properties, will be created for each breast, using a conductivity = 0.3 S/m. Subsequently, several microwave image parameters (features) will be used to quantify the images’ non-homogenous behaviour. A selection of these features is expected to allow for distinction between breasts with lesions (either benign or malignant) and those without radiological findings. For all the selected features, we will use Welch’s *t*-test to verify the statistical significance, using the gold standard output of the radiological study review.

## 1. Introduction

Current breast screening programmes for early cancer detection have been demonstrated to reduce breast cancer mortality; however, there is continuous discussion among the scientific community about several aspects of the current gold standard technique, mammography [1,2,3,4]. It is widely known that mammography (either 2D or recent developments such as digital breast tomosynthesis (DBT)) limits its use in population-based screening programmes to both a very specific age range and a limited screening frequency, usually biennial (the ECIBC’s Guidelines Development Group recently recommended women from 45 to 74 years of age [5] and the United States Preventive Services Taskforce recently drafted recommendations to include screening in women aged between 40 and 75 years of age [6]). Meanwhile, newer studies estimate that breast cancer (BC) is diagnosed in 6.6% of women younger than 40 years old [7], and around 20% of BC cases in Europe occur in women when they are below the age of 50 [8]. Overdiagnosis in screening, the use of ionising X-rays, and the cumulative effect it places on women have led to many controversies and discussions. Moreover, breast density is a big concern among radiologists as tumors may be mammographically hidden in dense breasts [9,10,11] or if the breast comprises small, elongated salt-like microcalcification particles [12]. In addition, the discomfort caused by breast compression and the performance reduction in dense breasts have motivated many researchers to investigate novel, safe techniques that overcome the mentioned limitations [13]. In this regard, microwave imaging has emerged as an interesting potential alternative to ionising-based techniques [14,15], based on the ability to discriminate between healthy tissues and tissues with lesions based on existing contrast in dielectric properties (permittivity and conductivity) within the microwave frequency spectrum.

This paper aims to present the approved clinical protocol for analysing one of these operational microwave systems, named MammoWave (developed by UBT Srl, Rivotorto di Assisi, Italy), which functions in air with only one transmitting and one receiving azimuthally rotating antenna, operating within the frequency band 1–9 GHz [16,17,18]. In contrast to mammography, the microwave exam is performed with the woman lying down on an examination table, in a comfortable prone position, without breast compression. The acquisition time of the system is roughly 7 min per breast.

For instance, this clinical protocol proposes a prospective multicentre international clinical trial to confirm the ability of MammoWave in breast lesions detection; it represents another step for finding suitable clinical applications through novel techniques such as microwave imaging, e.g., it represents a starting point prior to evaluating these kinds of systems in screening environments. Before starting such clinical trials, this detailed clinical protocol outlines all aspects of the study. Here, some of the key aspects of this protocol will be presented and discussed including its primary and secondary objectives and outputs, the inclusion and exclusion criteria, the number of participants to fulfil the required sample size, the statistical approach, the hospitals involved in the study, and the regulatory path followed. An overview of MammoWave’s current clinical validation status is also provided with a detailed description of the device. In more detail, to evaluate MammoWave in the framework of this clinical trial, microwave imaging will be performed on volunteers who have already gone through conventional exams and radiologists’ review to be used as the reference standard. For each breast of each volunteer undergoing this trial, our algorithm based on Huygens’ principle will be used to create a conductivity-weighted microwave image. Next, several microwave image parameters, i.e., features, will be calculated and used to measure and quantify the images’ non-homogenous behaviour. A selection of these features is expected to permit the distinction between breasts with radiological findings (WF) and those without any radiological findings (NF).

## 2. Experimental Design

### 2.1. Clinical Protocol

The sponsored prospective multicentre international clinical trial entitled “Clinical Investigation to Confirm the Ability of MammoWave in Breast Lesions Detection” was initiated (ClinicalTrials.gov Identifier: NCT05300464) with the aim of quantifying the capability of MammoWave in discriminating between breasts with no lesions or radiological findings (NF) and breasts with radiological findings (WF), that may be benign or associated with breast cancer. The protocol was designed following the SPIRIT reporting guidelines [19]. The study was approved by the Ethics Committee of CEAS Umbria (24197/22/AV, 9 March 2020), which acts as a coordinator, as it is the ethics committee to which Ospedale San Giovanni Battista—USL Umbria 2, Foligno, Perugia (Italy) refers. Additionally, the study was approved by the Ethics Committee of CER Liguria (337/2022, DB nr. 12281, 26 September 2022), which is the ethics committee to which Azienda Ospedaliera Universitaria IRCCS San Martino, Genova (Italy) refers. Concerning approval in Spain, the site (Complejo Hospitalario Universitario de Toledo, Servicio de Salud de Castilla—La Mancha) reviewed and accepted the approval of the coordinator.

### 2.2. Study Design

#### 2.2.1. Inclusion and Exclusion Criteria

Participants fulfilling all of the following inclusion criteria are eligible for the study:Signed informed consent form;Women;Adult ≥18 years old;Having a radiologist study output (to be considered as the reference standard) obtained using conventional exams within the last month. The conventional exam may be a breast specialist visit and mammography and/or ultrasound and/or magnetic resonance imaging, which will be integrated with the histological one if deemed necessary by the responsible investigator and when available;Volunteers willing to comply with the study protocol and recommendations;Women with intact breast skin (i.e., without bleeding lesions or scars);

The presence of any one of the following criteria will lead to the exclusion of the participant:Women who are participating in another clinical study;Women who belong to any vulnerable group (e.g., women with disabilities or impairments);Women with implanted electronic devices;Women who have undergone a biopsy less than one week before the MammoWave scan;Women with breast implants;Women with nipple piercings (unless they are removed prior to examination);Participation in other studies in the last month before screening;Pregnancy or breastfeeding.

#### 2.2.2. Primary and Secondary Objectives

The primary objective and expected outcome of this protocol is to generate empirical evidence for the detection of WF breasts (breasts with any kind of lesion, either benign or malignant) by using MammoWave and evaluating its sensitivity (number of ‘true positive’ results) against the reference standard (Figure 1). In addition, MammoWave’s safety and tolerability will be assessed as a safety objective.

The study’s secondary objectives are included in this protocol to further evaluate MammoWave’s performance by assessing: (1) the specificity of MammoWave in NF breast detection against the reference standard, (2) the sensitivity of the MammoWave device in breast lesion detection among different breast densities, (3) the sensitivity of MammoWave in women who had recently undergone a mammographic exam, (4) the sensitivity of MammoWave in breast cancer detection, (5) volunteers’ satisfaction after undergoing the MammoWave exam, and (6) both the specificity and sensitivity of MammoWave (against the reference standard) obtained retrospectively using MammoWave data from RadioSpin [20] technology simulator/artificial intelligence (AI) algorithms.

#### 2.2.3. Number of Participants

The study is composed of two phases: in the first phase, 15 participants in each centre all with NF breasts without any lesions will be examined by MammoWave. These data will be used to calibrate the image parameters’ thresholds for each apparatus installed at each centre. In the second phase, the remaining participants will be enrolled and examined by MammoWave, and the results will be compared against the reference standard collected by the clinical investigator.

According to the sample size calculation, considering that the primary objective of the study is to determine the ability of MammoWave to detect BL, it is anticipated that this study will enroll both patients with BL diagnosis and patients with NF, with a prevalence of BL patients of ~50%; of this 50%, about 50% will be BC patients. The required overall detection ability is 70% (all kinds of breast density). A minimum total number of 350 patients (175 with BL) is required to verify a sensitivity of 70% (H_1_) versus H_0_ = 60%, with an error of first type α = 0.05 and a power (1−β) = 80%. Note that BL includes malignant lesions related to breast cancer (BC) and benign lesions (both may be palpable or non-palpable lesions). BL also includes isolated clustered microcalcifications. Since it has been verified that the detection may depend on breast density and to generally increase the accuracy of the estimation process, the total number of patients to be enrolled has been increased to a maximum of 600. The volunteers’ enrolment started in February 2023 and will presumably last 12 months.

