### 3.2. Previous Clinical Studies

In a previous prospective clinical trial, a sensitivity of 82.3% and a specificity value of approximately 50% were achieved [17,26]; a retrospective analysis has also been performed, applying supervised machine learning (SML), enhancing specificity to >90% [27]. Figure 3a,b shows examples of obtained microwave images for a breast without any type of lesion and a breast with the described lesion, respectively.

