### 4.2. Statistical Analysis

For all of the selected features of the method given above, we will use the Welch’s *t*-test (i.e., a two-sample two-tailed unpooled variances *t*-test) with α = 0.05 to verify the statistical significance (*p* < 0.05), using the gold standard output of the radiological study review. For all the selected features of the method given above, we will also numerically evaluate the receiver operating characteristic (ROC); the area under the curve (AUC) will be also determined.

The performance of the proposed rule-of-thumb will be evaluated by empirically calculating the true positive rate, i.e., sensitivity (percentual estimates of true WF detection, with a 95% confidence interval), and the true negative rate, i.e., specificity (percentual estimates of true NF detection, with a 95% confidence interval), using the gold standard output of the radiological study review (excluding the first 15 patients of each site). Additional analysis will be performed through stratifying by breast density.

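### Sensitivity of 70% is called required, but the design tests only against 60%, and Section 4.2 attaches its 5% level to feature means instead of to that comparison

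*Protocol article*

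**What the plan says.** Section 2.2.2 makes sensitivity the primary objective: "evaluating its sensitivity (number of ‘true positive’ results) against the reference standard". Specificity is the first secondary objective.

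Section 2.2.3 describes the target in two ways. One sentence says "The required overall detection ability is 70% (all kinds of breast density"). The next says "A minimum total number of 350 patients (175 with BL) is required to verify a sensitivity of 70% (H_1_) versus H_0_ = 60" per cent, "with an error of first type α = 0.05 and a power (1−β) = 80" per cent. The total of 350 comes from doubling 175, "with a prevalence of BL patients of ~50" per cent. Enrolment is then raised to at most 600.

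Section 4.2 names one significance test, a "two-sample two-tailed unpooled variances" t-test at alpha = 0.05 on each selected feature, and adds a ROC curve and AUC per feature. Sensitivity and specificity of the combined rule follow as estimates with 95% confidence intervals, leaving out the first 15 women at each site. The section does not mention 60%, and it does not say what the sensitivity interval must show. The Abstract likewise names only the Welch test as the route to statistical significance.

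**The concern.** Two things do not fit together.

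- **The claim.** A trial that rejects 60% has shown sensitivity above 60%. It has not verified 70%. If 70% is a requirement, the null is in the wrong place. If 60% is the benchmark, 70% is only the planning assumption. As written, the same data could be reported as a success (60% excluded) or as a failure (observed value below 70%).
- **The place of the 5% level.** Section 2.2.3 attaches alpha = 0.05 to sensitivity. Section 4.2 and the Abstract attach it to feature means, with no adjustment across features. A significant feature difference could then be offered in support of the primary objective when it says little about sensitivity.

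**Working it through.** **Inputs.** Null 60%, alternative 70%, alpha 0.05, power 80%, 175 with lesions, maximum 600 (all Section 2.2.3); about 300 with lesions at 50% prevalence. Removing the 45 calibration women first leaves 555, about 277 with lesions. Sidedness is not stated.

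**1. Reproducing 175.** One-sample proportion, two-sided 5%:
- Arcsine: n = [(1.960 + 0.842) / (2·asin√0.70 − 2·asin√0.60)]² = 177.7, so 178.
- Normal approximation: n = [(1.960·√0.24 + 0.842·√0.21) / 0.10]² = 181.1, so 182.
- Normal-approximation power at 175: Φ[(0.10·√175 − 1.960·√0.24) / √0.21] = 78.6%.

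A one-sided 5% test gives 140 to 152 with the arcsine, normal and continuity-corrected formulas. The stated 175 therefore fits a two-sided 5% test, which matches a two-sided 95% interval compared with 60%.

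**2. What a pass requires.** Smallest count whose Clopper-Pearson lower 95% limit exceeds the benchmark:

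| n with lesions | Lower limit above 60% | 95% interval | Lower limit above 70% |
|---|---|---|---|
| 175 | 119 (68.0%) | 60.5% to 74.8% | 135 (77.1%) |
| 277 | 183 (66.1%) | 60.2% to 71.6% | 210 (75.8%) |
| 300 | 198 (66.0%) | 60.3% to 71.3% | 226 (75.3%) |

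Wilson limits move the 60% cut-off by at most one woman: 118/175 (67.4%), 183/277 and 197/300 (65.7%).

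**3. Probability of each result (exact binomial).**

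| n | Excludes 60%, true 70% | Excludes 60%, true 65% | Excludes 70%, true 70% |
|---|---|---|---|
| 175 | 74.7% | 22.7% | 2.2% |
| 277 | 93.1% | 38.1% | 1.9% |
| 300 | 94.1% | 38.3% | 2.4% |

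A device with a true sensitivity of 65%, short of the stated requirement, would pass the 60% null about one time in four at 175 and nearly two in five at 300.

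**4. What a significant feature test shows.** The group sizes are assumptions, because the article does not give breast counts. Take 277 breasts with findings (one per woman with a lesion) and 2·555 − 277 = 833 without, treated as independent and normal with equal variance. The just-significant standardised difference is d = 1.96·√(1/277 + 1/833) = 0.136. Then AUC = Φ(d/√2) = 0.54, and single-feature sensitivity at a cut-off on the median of the no-finding group = Φ(d) = 55%. With 277 v 278 these become 0.55 and 57%; with 175 v 130, 0.56 and 59%. In each case a feature is significant while its own sensitivity at that cut-off is below 60%. Section 4.1 names five features. Unadjusted, the chance of at least one false positive is at most about 1 − 0.95⁵ = 22.6%, reached if the tests were independent and lower if they are positively correlated.

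**The case against.** The strongest reply is that the interval planned in Section 4.2 already carries the test. Comparing its lower limit with 60% is the two-sided 5% test that 175 fits, and a condensed article may leave the decision rule to a fuller document. Also, no section makes the Welch tests a success criterion: Section 5 lists feature discrimination as a goal alongside the primary and secondary objectives.

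Much of this stands. A reader might infer that sensitivity is never tested. The documents do not support that: an analysis able to carry the test is planned, and what the article lacks is the link to 60%. Nor does it follow that the sponsor intends to declare success from feature means. The reply does not remove the conflict inside Section 2.2.3, or the fact that the only significance test in Section 4.2 and the Abstract concerns something other than the primary endpoint.

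A reader might also infer that passing on sensitivity would show no discrimination, since "the specificity of MammoWave in NF breast detection against the reference standard" is only secondary and the previous prospective trial is reported with "a specificity value of approximately 50% were achieved". The documents do not support this either. Specificity with a 95% interval and feature AUCs are planned beside sensitivity. Section 4.1 sets thresholds at the site median of lesion-free women and requires at least five positive scores, so with five features an uninformative device would call at most about half of breasts positive. In a simulation of no discrimination (three sites, medians from 15 or 30 breasts, 175 breasts with findings), the chance of reaching 119/175 was about 0 at feature correlation 0.5 or 0.9, and 0.2% to 1.1% with perfectly correlated features. That protection assumes that five features are used (the text says four but names five) and that the calibration women resemble the later lesion-free women. A joint success condition on sensitivity and specificity would be a preference, not a correction.

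**Conclusion.** The point holds as an inconsistency about what success means. The design supports a claim of sensitivity above 60%, reached at an observed 66% to 68%. It cannot realistically verify 70%, since that has about a 2% chance when 70% is true. Section 4.2 needs to connect its sensitivity interval to the 60% null and separate the feature tests from the primary objective.

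The cut-offs and probabilities assume independent binomial observations, one per woman with a lesion, and a two-sided 95% interval. The Figure 1 legend describes a comparison for each breast, so within-woman correlation would widen the interval if the analysis is per breast. The feature-test figures in step 4 rest on assumed breast counts and are illustrative only.

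**What to change.** - **Section 4.2:** state that the primary criterion is a lower limit of the two-sided 95% confidence interval for sensitivity above 60%, name the interval method, allow for two breasts per woman if the analysis is per breast, and limit the claim to sensitivity above 60%.
- **Section 2.2.3:** describe 70% as the assumed sensitivity under the alternative, not as required or to be verified.
- **Section 4.2 and Abstract:** label the Welch tests on features exploratory and say that they are not evidence for the primary objective.
- **Power:** restate it for the chosen rule. With Clopper-Pearson limits it is about 75% at 175, not 80%, and about 94% at 300, before any clustering.

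The cost is wording and a weaker permitted claim. No enrolment beyond the planned maximum of 600 is needed if recruitment approaches that figure. Stopping near the minimum of 350 would leave exact power below the stated 80%.

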## Figures and Tables

**Figure 1 diagnostics-13-02100-f001:**
[figure not shown]
The clinical trial’s workflow. For each breast of each subject, the microwave imaging output of MammoWave will be compared to the output of the radiologist study review (from conventional exams).

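### The 60%/70% sensitivity test is sized on 175 patients with lesions but scored per breast, and nothing links the two units

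*Protocol article*

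**What the plan says.** The sample-size text in section 2.2.3 counts people. It reads "A minimum total number of 350 patients (175 with BL) is required to verify a sensitivity of 70" (per cent), sets the hypotheses as "a sensitivity of 70% (H_1_) versus H_0_ = 60" (per cent), and plans the test "with an error of first type α = 0.05 and a power (1−β) = 80" (per cent). The case mix is also in people: "with a prevalence of BL patients of ~50%; of this 50%, about 50% will be BC patients". Enrolment may go further: "the total number of patients to be enrolled has been increased to a maximum of 600".

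The endpoint is defined in breasts. Section 2.2.2 states the primary objective as "to generate empirical evidence for the detection of WF breasts (breasts with any kind of lesion, either benign or malignant"). Section 2.2.5 classes each breast as NF at BI-RADS 1 and as WF at any other score, including 2 (benign). Section 4.1 computes the binary scores for each breast and issues the final call for a breast. The Figure 1 caption fixes the comparison: "For each breast of each subject, the microwave imaging output of MammoWave will be compared to the output of the radiologist study review". Section 4.2 reports sensitivity as the percentage of true WF detected, with a 95% confidence interval.

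No section names an index breast, combines two breast results into one result per woman, or restates the 60%/70% test or the cancer mix in breasts.

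**The concern.** A sensitivity test needs one denominator. Here 175 women with lesions equal 175 WF breasts only if none of them has findings in both breasts. Because a benign score of 2 already makes a breast WF, findings in both breasts are plausible.

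Three things then move away from the plan:

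- The number of units is no longer 175.
- The units are no longer independent, because two breasts of one woman tend to give similar results.
- The cancer share is no longer one half, because a second benign breast adds to the benign side only. Section 2.2.2 lists sensitivity for cancer as a separate objective, so the protocol itself allows that it may differ from the pooled figure.

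At stake are the meaning of the stated 80% power and the validity of the interval set against 60%. If the unit stays open until results are known, it could also be chosen after seeing them.

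**Working it through.** **Inputs from the protocol article.** Section 2.2.3: 175 women with BL, about half with cancer (87.5), H0 60%, H1 70%, α 0.05, power 80%, maximum enrolment 600. Sections 2.2.3 and 4.2: 15 calibration women per site at three sites (45) are left out of the sensitivity estimate.

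**Assumptions, not in the article.** The share q of BL women with both breasts WF; the within-woman correlation ρ; one cancer breast per cancer patient.

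**1. The plan's own figure.** One-sample test of a proportion, one outcome per woman. The article does not state sidedness; 175 fits a two-sided test.
- Arcsine formula: n = (1.96 + 0.84)² / (2·asin√0.70 − 2·asin√0.60)² = 177.7, so 178.
- Normal-approximation power at n = 175: Φ[(0.10·√175 − 1.96·√0.24)/√0.21] = 78.6%.
- Binomial probability of at least 118 of 175 (the two-sided normal critical value) at 70%: 79.6%.
- 175/0.50 = 350.

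The figure reproduces closely with one independent outcome per woman.

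**2. Denominator and mix per breast.** WF breasts = 175(1+q). Cancer share = 87.5/[175(1+q)] = 0.5/(1+q).

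| q | WF breasts | Cancer share |
|---|---|---|
| 0 | 175 | 50% |
| 10% | 192.5 | 45% |
| 30% | 227.5 | 38% |
| 50% | 262.5 | 33% |
| 100% | 350 | 25% |

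**3. Pairing, with sensitivity held at 70%.** Design effect = 1 + 2qρ/(1+q). Effective n = 175(1+q)/design effect. Actual two-sided error of an unadjusted test = 2[1 − Φ(1.96/√design effect)]. At q = 30%:

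| ρ | Design effect | Effective n | Power | Error if pairing ignored |
|---|---|---|---|---|
| 0 | 1.000 | 227.5 | 88% | 5.0% |
| 0.3 | 1.138 | 200 | 84% | 6.6% |
| 0.5 | 1.231 | 185 | 81% | 7.7% |
| 1 | 1.462 | 156 | 74% | 10.5% |

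**4. Illustration where sensitivity moves with the mix.** Assume 80% for cancer breasts and 60% for benign breasts, which average 70% at the planned mix. Pooled sensitivity = 0.6 + 0.2 × cancer share. Breasts are treated as independent, and power is the binomial tail beyond the normal critical value.
- q = 25%: cancer share 40%, sensitivity 68%, 219 breasts, power 69%.
- q = 50%: cancer share 33%, sensitivity 66.7%, 262 breasts, power 61%.

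The same breast counts with sensitivity held at 70% give 87% and 93%. At maximum enrolment, 600 − 45 = 555 women, half with BL, is 277.5 women, hence 347 and 416 WF breasts. The power under the 80%/60% split is then about 86% and 79%.

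**The case against.** The strongest reply is that the endpoint is defined once, per breast, and consistently so. Section 2.2.3 is a recruitment target, and it is women who are recruited. It never calls 60% or 70% a per-patient sensitivity. If each woman with a lesion has one WF breast, both the hurdle and the mix carry over. The article is also condensed, and the handling of paired breasts often sits in the analysis plan.

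Much of this stands. The 175/350 arithmetic is sound, and silence about pairing alone would be no finding in an article. But the article does more than stay silent: it gives the hypothesis, denominator and case mix in one unit and the endpoint in another. Whichever unit a fuller document chose, a per-breast analysis would need the stated power and mix restated unless no woman had bilateral findings, and the article does not say so.

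A reader might infer two stronger things:

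- **That a flag on the healthy breast could count as detecting a lesion in the other one, so that an uninformative device could pass.** No section contains such a rule. The breast-by-breast comparison in Figure 1 and the per-breast call in section 4.1 speak against it.
- **That the trial is underpowered.** The 69% and 61% in step 4 need an assumed 80%/60% split and assumed bilateral shares, and apply only to the minimum sample. Nothing in section 2.2.3 derives 70% from the half-cancer mix. With 70% held fixed, extra WF breasts raise power unless the correlation is very high.

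**Conclusion.** The mismatch is in the text and unresolved in the article. The size of its effect depends on q and ρ, which the article does not give. At q = 30% the analysed denominator is about 228 rather than 175. The cancer share is about 38% if each cancer patient has one cancer breast. An interval that ignores pairing has a two-sided error of about 6.6% to 7.7% for correlations of 0.3 to 0.5. At q = 0 all three effects vanish.

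The direction of the power change is not determined. What can be said is that the stated 80% belongs to 175 independent outcomes, one per woman, and not to a per-breast analysis with bilateral findings. The point merits a change because the unit of the primary test should be fixed before results are seen.

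**What to change.** In sections 2.2.3 and 4.2, name one unit for the 60%/70% test and restate the power in it. Either option works:

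1. **All WF breasts**, which keeps the objective in section 2.2.2. Use an interval clustered by woman, and state the assumed share of bilateral findings and the within-woman correlation behind the power. The expected cancer share should be given per breast.
2. **One prespecified index WF breast per woman with BL**, for example the breast with the higher BI-RADS score, with a fixed rule for ties. This keeps 175 independent units and the planned mix of about half cancer, so the existing calculation carries over. Sensitivity over all WF breasts becomes a secondary analysis.

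In both, say that a true positive requires a WF call on that same breast.

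The cost is wording. Section 2.2.5 already records the side assessed and the BI-RADS classification of breasts. Option 1 also needs two planning assumptions and a clustered interval. The downside of option 2 is real: second WF breasts leave the primary estimate, and if lower-scored breasts are harder to detect, that estimate will be higher than the one over all WF breasts.
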